##### Having a Craving?

This module is a brief behavioral experiment in which the participant is prompted to rate the intensity of their craving on a scale from 0 to 10 and set a timer for 5, 10, or 20 minutes, during which time they are instructed to do something else. Participant has the option of playing Tetris on their device, as there is some evidence that playing Tetris acts as visual cognitive interference and reduces the incidence and intensity of cravings in real-world settings [23]. When the timer finishes, the participant receives a text message prompting them to return to the exercise and rerate their craving, after which they can repeat the exercise or move on to another module.

##### High-Risk Situations

This module includes a series of questions designed to assist the participant to identify potential high-risk situations and make a plan to cope with them without using methamphetamine. Possible strategies include avoiding the situation altogether when possible, making a plan to leave if things get hard, rehearsing how to say no to people when drugs are offered, preparing by letting people know that they have decided not to use, having support people nearby/contactable, and reminding themselves of their primary motivation for reducing or stopping use.

##### Slip-Ups

In this module, slip-ups are differentiated from relapse and reframed as an opportunity for learning and getting stronger for next time. Unhelpful and helpful thoughts are articulated, and then a series of questions prompts the participant to reflect on how they were feeling and what they were doing and thinking to enable them to respond differently next time.

##### Quiet Reflections

This module contains a series of reflections and mindfulness exercises that may be selected from a launch page within the module. These reflections emphasize connection to culture, community, and identity and provide pathways for addressing culturally situated grief and loss and connecting with cultural programs. The module also contains a basic introduction to mindfulness via psychoeducation and a brief breathing exercise taken from Smout and Lazicki [19].

##### Building Up the Positive

Building up the Positive is an adapted version of the Bullseye Values Survey developed by Lundgren et al [24] and further popularized by Harris [25]. This exercise does not focus on drug use specifically and is intended to help the participant build a valued life outside of their use. In our adapted version, the participant is presented with three baskets labeled less important, important, and very important. Values appear on the screen and the participant sorts them into the appropriate basket. In the next stage of the exercise, those values rated as very important appear one by one and can be placed on a stylized image of a dartboard—close to the center if the participant feels they are living well in accordance with that value and further away from the center if they are not living in line with that value. Once all the values have been placed on the board, participant is encouraged to select a value placed further from the center to work on in the next section. Participant is then asked to write a specific, achievable action that would help them move closer to living out that value. This is followed by three questions: What would be the first step toward this goal? Who could help you do this? When will you do this? After nominating a day and time, participant has the option to send a text message to themselves reminding them to take the first step. Participant can then choose to work on another value, print their plan, or select another module.

#### Incorporation of Feedback From Focus Testing

The modules were focus tested in two phases. The first module developed (Are You Ready?) was focus tested with Aboriginal people with past or current experience of methamphetamine use recruited via organizational networks in urban and regional locations in South Australia and Victoria. Feedback from these groups was incorporated into the WBTP and informed the further development of subsequent modules. Later modules were focus tested with participants recruited via the same networks. Feedback was generally positive and supported the use of films to convey key messages. Participants found the content credible and useful and provided advice to improve the clarity of terminology, imagery, and usability. They also noted that while films are a powerful medium for conveying positive messages, the emotive nature of some stories could be triggering for some people, which prompted a greater focus on building safety measures into the online intervention—for example, ensuring timely access to face-to-face support when needed.

### Outcome Measures

#### Primary Outcome

The primary outcome measured will be the number of days the participant used methamphetamine during the treatment phase, assessed using questions from the Australian Treatment Outcome Profile (ATOP) [26]. The ATOP has been validated in treatment settings across Australia.

#### Secondary Outcomes

Differences in help-seeking will be assessed with the General Help-Seeking Questionnaire [27] and by the rate of referral and frequency, type, and duration of health service contact resulting from use of the online intervention. Other outcomes will include readiness to change (Readiness to Change Questionnaire) [28]; psychological distress (Kessler 10) [29]; poly-drug use during the past month (ATOP) [26]; severity of dependence (Severity of Dependence Scale) [30]; days out of role (referencing methamphetamine use rather than depression) [31]; and usability and acceptability (Internet Intervention Adherence Questionnaire [32], which includes questions about barriers and facilitators to using the program and optional free-text to report any criticisms or other feedback). Feasibility of the online intervention will be assessed overall by demographics of participants, general uptake and use of the online intervention (modules completed, time spent, etc), and number of participants who complete the program. Qualitative interviews with health service staff and at least two online intervention users will be conducted to explore positive and negative experiences.

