### Objective

Our primary hypothesis is that participants who complete the We Can Do This online intervention will have significantly reduced days of methamphetamine use in the last 4 weeks at 1, 2, and 3 months from baseline compared with wait-listed participants with access to treatment as usual. Our secondary hypothesis is that the program will increase intended and actual help-seeking, including attendance at participating health services.

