**Figure 1 figure1:**
[figure not shown]
Flow of participants through the We Can Do This trial. AOD: alcohol and other drugs; MH: mental health.

Participants will have the option of receiving health practitioner support via weekly phone calls from trained staff at the participating health service in their geographical area. If this option is selected, participant contact details will be forwarded to the relevant health service, and they will receive an introductory phone call during which the health practitioner will explain their support role and schedule the weekly contact. Alternatively, participants will have the option to proceed without practitioner contact. In either case, participants will be prompted to consider the option of talking to someone at several points within the online intervention.

At the end of each module, printable summary pages of their inputs may be emailed to participants, their support people, and members of their Healing Circle as attachments according to participant preferences. With the participant’s permission, this summary may also be emailed to their allocated practitioner, if they have one. Participants will be sent an email or text to remind them to log in each week regardless of which modules have been completed. If all modules are completed early, participants may repeat modules. All online interactions will be monitored and inputs recorded but de-identified prior to analysis.

The online intervention has been developed so that a range of health practitioners may provide optional clinical support as an adjunct to the program. Health practitioners providing support will have received face-to-face training from the research team and a training manual with detailed instructions in the use of the online intervention and how it may be used as the basis for supportive conversations that consolidate the online intervention content. The manual contains examples of scripts to guide conversations. If issues arise in these conversations that fall outside the practitioners’ professional boundaries, they will have clear referral pathways available to them. Ongoing support for health practitioners will be provided throughout the trial by the research team and senior clinicians in each organization.

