### Data Collection and Management

Data will be collected online at baseline, and at 1, 2, and 3 months postbaseline. Participants will be invited to complete follow-up assessments online via a link sent by email and/or text message in the first instance and followed up by telephone thereafter. For analysis, participants will be assigned a unique patient identifier. De-identified data on rate of referral and frequency, type, and duration of health service contact resulting from use of the online intervention will be provided by the health service using the unique patient identifier allocated to each participant. Data collected online will be de-identified and uploaded automatically to a secure server managed by the primary sponsor (South Australian Health and Medical Research Institute) in accordance with strict research governance protocols [35]. Contact details are necessary for the successful operation of the online intervention but will not be stored with data collected for research purposes. Access to data will be limited to research staff named on the ethics protocol.

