### Statistical Analyses and End Points

An intention-to-treat analysis will compare the primary and secondary outcomes for the intervention versus placebo conditions at 1, 2, and 3 months from baseline. Main effects will be evaluated using a mixed effect model that accounts for site-specific clustering effects.

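### The service-contact measure of help-seeking counts only contact attributed to the programme, so controls score zero by definition and the attendance part of the secondary hypothesis cannot be tested

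*Protocol article*

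**What the plan says.** The Objective section states the hypothesis at issue: "Our secondary hypothesis is that the program will increase intended and actual help-seeking, including attendance at participating health services".

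Secondary Outcomes gives two routes to it. The first is a questionnaire: "Differences in help-seeking will be assessed with the General Help-Seeking Questionnaire". The second is service activity, assessed "by the rate of referral and frequency, type, and duration of health service contact resulting from use of the online intervention". Data Collection and Management repeats the restriction when it describes what the services will send: "health service contact resulting from use of the online intervention will be provided by the health service using the unique patient identifier". The limit to programme-related contact thus governs both the outcome definition and the data request.

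Trial Design withholds the programme from the wait list until the 3-month control period is over and plans no research assessments of that group afterwards. Until then controls take the same assessments as the intervention group and can use alcohol and other drug counselling at the participating service. Statistical Analyses and End Points says that an intention-to-treat analysis "will compare the primary and secondary outcomes for the intervention versus placebo conditions" at 1, 2 and 3 months.

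The Implementation section offers intervention participants weekly calls from trained staff of the local participating service: "If this option is selected, participant contact details will be forwarded to the relevant health service". The calls are optional, and expected uptake is not given.

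**The concern.** A randomised comparison needs an outcome that can occur, and is recorded in the same way, in both arms. This one is conditional on using something that only one arm has. A control who sees a counsellor every week for 3 months scores zero; an intervention participant with one contact attributed to the programme scores one.

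The hypothesis concerns the net effect: whether people offered the programme attend services more than they otherwise would have. A count of attributed contacts cannot answer that. Someone recorded as having come through the programme might have come anyway, and programme-linked contact might replace ordinary attendance. Only the control arm's total contact can show this, and the definition leaves that total out.

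The Discussion gives linkage to face-to-face support as one of three main ways in which the programme would bring benefit. A between-arm result on this measure would be the natural evidence for that claim, and it would have no valid comparator.

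**Working it through.** **1. The definition against the design.**
- Rule (Secondary Outcomes; Data Collection and Management): contact counts only if it results from using the programme.
- Control access (Trial Design): none before month 3, and no research assessments after it.
- Comparison times (Statistical Analyses and End Points): months 1, 2 and 3.
- Result: control value = 0 by definition and intervention value ≥ 0, so the difference is ≥ 0 whatever the true effect on attendance.

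**2. The article's own numbers.** It gives no figure for this outcome. The only sizes available come from Sample Size and Power: 100 evaluable per group and 144 recruited. With 30% attrition, 100 / 0.70 = 142.9, or 143, against 144 stated; this agrees to within one participant. I use 100 and 144 per arm below.

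**3. How few attributed contacts make a difference significant.** With k of n in the intervention arm and 0 of n in controls, the two-sided Fisher p is 2 × C(n,k) / C(2n,k).

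| k | n = 100 | n = 144 |
|---|---|---|
| 5 | 0.059 | 0.060 |
| 6 | 0.029 | 0.030 |
| 8 | 0.0068 | 0.0071 |

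Six participants suffice for p < 0.05 and eight for p < 0.01.

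**4. How likely that is.** Let u be the share of the intervention arm with at least one attributed contact (an assumption; no source in the article). The chance of p < 0.05 is P(X ≥ 6) with X ~ Binomial(n, u).

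| u | n = 100 | n = 144 |
|---|---|---|
| 5% | 38% | 73% |
| 10% | 94% | 99.7% |
| 20% | >99.9% | >99.9% |

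Total attendance in the two arms does not enter this calculation. For scale, if 20% of 144 controls attended counselling (assumed), 0.20 × 144 = 28.8, so about 29 attenders would be recorded as zero.

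**5. Would removing the attribution wording be enough?** Suppose all contact is counted in both arms, background contact q is equal, and support calls also count, with uptake u independent of background contact (all assumed). The intervention proportion is 1 − (1 − q)(1 − u). At q = 20% this is 28%, 36% and 44% for u = 10%, 20% and 30%, against 20% in controls. The chance of two-sided p < 0.05 (normal approximation for two proportions) with no change in ordinary attendance is:

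| q | u | n = 100 | n = 144 |
|---|---|---|---|
| 10% | 10 / 20 / 30% | 44 / 91 / >99% | 58 / 98 / >99% |
| 20% | 10 / 20 / 30% | 26 / 72 / 96% | 36 / 86 / 99% |
| 30% | 10 / 20 / 30% | 18 / 54 / 86% | 24 / 69 / 96% |

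If the calls were counted, correcting the attribution wording alone would leave a difference produced by delivery of the intervention. The calls need to be identifiable and reported apart.

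**The case against.** The best defence is that attributed contact is a process measure. Secondary Outcomes also lists usability, modules completed and time spent, which cannot exist in controls before month 3, so the one-sentence plan to compare secondary outcomes cannot apply literally to every item. That is fair as far as it goes. But the service-contact measure stands in the sentence on differences in help-seeking, feasibility and uptake are listed separately, and no other measure described draws on the services' own records of attendance. A later analysis plan could not recover control contacts that were never requested.

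Three stronger readings are tempting and should not be drawn.

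- *The secondary hypothesis is confirmed by construction.* The documents do not support this. The hypothesis also covers intended help-seeking, and the General Help-Seeking Questionnaire is not conditional on the programme and is among the assessments that both arms take. Even on the service-contact measure a positive result needs some uptake: at 5% the chance of p < 0.05 is 38% to 73%.
- *The trial counts its own support calls as help-seeking.* The text neither includes nor excludes them. Contact type is to be recorded, which could allow separation. Choosing optional support might also be regarded as help-seeking; separate reporting leaves both views open.
- *Services cannot report on controls.* Contact details are forwarded to arrange calls, but the article does not say that this is the only route to linkage. Data Collection and Management describes an identifier allocated to each participant, without limiting it to one arm. Linkage detail may also sit in the full protocol.

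The main point needs none of these: the definition alone excludes controls.

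**Conclusion.** The point holds for the service-contact component of help-seeking. As defined, it is zero in controls throughout the comparison period, omits their treatment-as-usual counselling, and can only favour the intervention. It cannot test whether "the program will increase intended and actual help-seeking, including attendance at participating health services" as far as actual help-seeking and attendance are concerned. This conclusion follows from the text and rests on no assumed rate.

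The size does rest on assumed rates. Six attributed contacts against a structural zero give p of about 0.03, and with 10% of the intervention arm having one, a significant difference is 94% to 99.7% likely. Possible inflation from support calls is a risk left open by the wording and is not a stated rule.

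Severity is moderate. The primary outcome, the sample size, randomisation and the questionnaire-based outcomes are untouched.

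**What to change.** In Secondary Outcomes and in Data Collection and Management, define the between-arm outcome as all contact with participating services from randomisation to 3 months, recorded identically in both arms whatever prompted it. Obtain it either from the service extract by participant identifier, requested for every participant in both arms, or from one self-report service-use item in the 1-, 2- and 3-month questionnaires.

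Report support calls delivered as part of the intervention separately. Keep referrals and contact attributed to the programme as a descriptive process measure in the intervention arm, outside the between-arm comparison.

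The cost is a change of wording plus a slightly larger data request to services or one extra questionnaire item. It should be settled before recruitment starts, because control-arm contact that is not requested at the time may be hard to recover.

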### Sample Size and Power

Based on our previous research, we expect a baseline mean of 16 days methamphetamine use in the past 4 weeks [33]. We aim to detect a reduction to a mean of 8 use days in the past 4 weeks, as this will have a significant clinical impact in terms of reducing the risk of psychotic symptoms and violence (reduction from odds of 10-11 to 2-3) [33,34]. To detect this difference at each of the follow-up points with 90% power at a *P*<.01 level, we will require a sample of 100 participants per group. Based on our previous research, with assertive follow-up (ie, by phone as well as by email/text) we expect up to 30% attrition at follow-up, meaning that we will need to recruit 144 participants into each condition (intervention and treatment as usual) or a total of 288 participants. Treatment sites will be ACCHSs and other relevant services with Aboriginal clients.

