**Methods:**

Participants will be Aboriginal and Torres Strait Islander people aged 16 years and over who have used methamphetamine at least weekly for the previous 3 months. They will be recruited online and via health services. During the intervention phase, participants will have access to the online intervention for 6 weeks with optional telephone or face-to-face support provided by participating health services. The primary outcome measure will be the number of days the participant used methamphetamine over the past 4 weeks compared to wait-list controls, assessed at baseline, 1, 2, and 3 months. Secondary outcomes will include help-seeking, readiness to change, severity of dependence, and psychological distress. Any important changes to the protocol will be agreed upon by the trial management committee and communicated to all relevant parties, including trial site representatives and the trial registry.

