A systematic review of psychological treatments applied specifically to methamphetamine use concluded that good clinical outcomes are achieved with cognitive-behavioral therapy (CBT) [9]. Further, CBT with or without motivational interviewing appears to be associated with reductions in methamphetamine use and other positive changes [9]. A preliminary randomized controlled trial comparing acceptance and commitment therapy (ACT) and CBT indicated that these two therapeutic modalities produce comparable results; therefore, ACT may be a viable alternative to CBT for treating harmful methamphetamine use [10]. This is relevant in an Aboriginal context where written, worksheet-based CBT approaches are not always preferred for a range of reasons including literacy and a cultural preference for approaches incorporating yarning and story-telling [11].

Internet interventions have shown effectiveness for some substance use problems, including methamphetamine use. For example, Breaking the Ice was a fully automated, participant self-guided, Web-based intervention consisting of six self-administered modules incorporating components of CBT and motivational interviewing [12]. The program was effective at increasing help-seeking and participant motivation to reduce their methamphetamine use and reducing days out of role, relative to a wait-list control (at 3 to 6 months from baseline). Effect sizes were small to moderate (relative risk 0.5-0.74) [13]. The program participants who completed the Web-based modules, predominantly non-Aboriginal and male, showed a nonsignificant reduction in their methamphetamine use [13]. Feedback on the acceptability of Breaking the Ice was generally positive in relation to the use of fictional case stories as an engaging approach, but participants reported that the program was also too text-heavy, which may have contributed to attrition (less than half [48%] completed all three modules).

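### The 100 per group cannot be reproduced from the printed inputs, and the 8-day target is a fall from baseline rather than the between-group difference the trial tests, so the 90% power is unsupported

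*Protocol article*

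**What the plan says.** The protocol article's section Sample Size and Power gives these elements:

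- Starting point: "we expect a baseline mean of 16 days methamphetamine use in the past 4 weeks".
- Target: "We aim to detect a reduction to a mean of 8 use days in the past 4 weeks".
- Requirement: "To detect this difference at each of the follow-up points with 90% power", at a P<.01 level.
- Result: "we will require a sample of 100 participants per group", raised to 144 per group (288 in total) for up to 30% attrition.

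The section prints no SD, no sidedness, no wait-list mean at follow-up, and no allowance for clustering or for the three time points.

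The comparison to be tested is between groups. The Objective section sets the intervention "compared with wait-listed participants with access to treatment as usual", and the abstract defines the primary outcome as the "number of days the participant used methamphetamine over the past 4 weeks compared to wait-list controls". Statistical Analyses and End Points compares the conditions at 1, 2 and 3 months with a mixed model that accounts for site.

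**The concern.** Two things do not fit.

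First, a drop from 16 to 8 days is large on a scale that runs from 0 to 28. It should need far fewer than 100 per group, even at a P<.01 threshold. Either an input was left out of the text or the number came from a different calculation.

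Second, the effect is described as a change from the expected baseline mean, but the trial tests intervention against wait-list at follow-up. The two are the same only if wait-list participants average 16 days for the whole 3 months. Under Trial Design, those participants complete the same assessments and can use alcohol and other drug counseling. Under the eligibility section, everyone enters because of recent frequent use. Some fall in the control arm is therefore plausible, and the section does not say what was assumed.

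This paragraph is the only justification of the trial's size for the primary outcome. As it stands, a reader of a null result cannot tell which between-group difference the trial was able to exclude.

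**Working it through.** **Inputs from the document.** Means 16 and 8 days, so a difference of 8; power 90%; alpha .01; 1:1 allocation; 100 per group; attrition 30%; outcome a count of days in 4 weeks, so 0 to 28. **Assumed:** a two-sided test, and SDs of 8, 9 and 10 where an SD is needed, because none is printed.

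**1. Trying to reproduce 100 per group.**

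n per group = 2 × (z₀.₉₉₅ + z₀.₉₀)² × (SD/8)² = 2 × (2.576 + 1.282)² × (SD/8)² = 29.76 × (SD/8)².

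Setting n = 100 gives SD = 8 × √(100/29.76) = 14.67 days.

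**2. Is that SD possible?** On a 0–28 scale with mean m, the largest SD is √(m(28 − m)), reached only if everyone reports 0 or 28 days.

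- m = 16: √(16 × 12) = 13.86
- m = 8: √(8 × 20) = 12.65
- pooled: √((192 + 160)/2) = 13.27
- any mean: at most 14

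So 14.67 is out of reach. At the pooled ceiling, n = 29.76 × (13.27/8)² = 82 per group.

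**3. Variants.** The SD needed for 100 per group, against the pooled ceiling of 13.27:

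| Variant | SD needed | Attainable? |
|---|---|---|
| One-sided .01 | 15.68 | no |
| t-test instead of normal approximation | 14.54 | no |
| Rank test, efficiency 0.955 / 0.864 | 14.33 / 13.63 | no |
| Bonferroni, .01/3 | 13.42 | no (just above) |
| Joint 90% over three visits, taken as independent | 12.87 | yes, near the ceiling |
| Joint 90% plus Bonferroni | 11.90 | yes |

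Treating 16/28 and 8/28 as proportions gives 87 per group, 94 with continuity correction and 76 one-sided; none is 100. A design effect would also close the gap: 100/82 = 1.22 at the ceiling, or 100/(29.76 × (10/8)²) = 100/46.5 = 2.15 at an SD of 10. None of these additions is stated.

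**4. Attrition.** 100/0.7 = 142.9, against 144 stated (144 × 0.7 = 100.8). This step is acceptable.

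**5. What 100 per group delivers** (two-sided .01, t-test, no clustering, no baseline adjustment):

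| Between-group difference | SD 8 | SD 9 | SD 10 |
|---|---|---|---|
| 8 days (controls stay at 16) | >99.8% | >99.8% | >99.8% |
| 4 days (controls at 12, intervention at 8) | 82% | 71% | 59% |
| 3 days | 52% | 41% | 32% |

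For a true 8-day difference, power is still 95% at the pooled ceiling SD of 13.27, and only 32, 40 and 49 per group would be needed for 90% at SDs of 8, 9 and 10.

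**6. Detectable difference.** At 90% power, 100 per group detects about 0.55 SD: 4.4, 4.9 and 5.5 days at SDs of 8, 9 and 10. If the intervention arm reaches 8 days, the control mean must therefore stay at or above about 12.4, 12.9 and 13.5. Power drops below 90% once controls fall by more than about 3.6, 3.1 and 2.5 days from 16.

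**The case against.** Several points on the other side have force.

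**An unstated allowance could explain 100.** The text asks for power at each follow-up point, which might mean joint power over three visits, and the analysis model allows for site clustering. Either could bring the SD into the possible range. This stands: a reader might infer that no SD at all can lead to 100 per group, but that holds only for a single comparison with no such allowance. It does not rescue the printed calculation, which mentions neither.

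**The trial may exceed its stated power.** A reader might also infer that the 90% is wrong in the sense that the trial is underpowered. The document does not support that. If 8 days is the true between-group difference, 100 per group gives at least 95% before clustering. Shortfalls appear only if controls improve enough or clustering inflates the variance enough, and the article has no figure for either.

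**The pre-post wording may be shorthand.** The section speaks of a difference and of numbers per group, so its authors may simply have assumed controls stay at 16. That is a fair reading, but it makes the assumption decisive and leaves it unstated. The Background remark that completers of an earlier web program "showed a nonsignificant reduction in their methamphetamine use" gives no effect size and says nothing about change in controls, so no weight is put on it here.

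**The lower power figures are conditional and unadjusted.** Baseline adjustment would help. With an assumed baseline correlation of 0.5, the 4-day figures become roughly 93%, 85% and 75%. This stands.

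**An article condenses.** An SD or design effect may be in the full protocol, so its absence alone is not a fault. The point rests on the printed figures not fitting together.

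**Conclusion.** The point holds in a limited form. Under a standard two-sample calculation, the printed inputs give 100 per group only at an SD of 14.67, above the 13.27 pooled maximum (14 for any mean) of a 0–28 day outcome. Some unprinted allowance must have been applied, or the figure is an error. Separately, the effect used is a fall from baseline, and it matches the tested contrast only if wait-list controls do not change.

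The stated 90% is therefore unsupported in either direction: at least 95% before clustering if the between-group difference is truly 8 days, and below 90% if controls improve by more than about 2.5 to 3.6 days while the intervention arm reaches 8. The second statement rests on assumed SDs of 8 to 10, a two-sided t-test, no clustering and no baseline adjustment. Underpowering is a possibility, not a demonstrated fault. The justification should be corrected, but nothing here shows that the recruitment target has to change.

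**What to change.** Keep 288 and rewrite the justification around the contrast that will be tested:

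- State the between-group difference detectable with 100 per group at 90% power and two-sided P<.01. That is about 0.55 SD before any clustering allowance or baseline adjustment, or 4.4 to 5.5 days if the SD is 8 to 10.
- Take the SD from the sponsor's own prior data. The 8 to 10 range used here is illustrative and should not be copied into the plan.
- State the wait-list mean assumed at each follow-up.
- State any inflation factor applied for joint power, multiplicity or site clustering. If there was none, delete the claim that a 16-to-8 reduction requires 100 per group.

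Once the SD, the control mean and any clustering allowance are known, check that the resulting detectable difference is one the investigators regard as worthwhile. The cost is a rewritten paragraph and a matching registry update if the registry repeats the calculation; no extra participants and no change to trial conduct.
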